#### PK11195-PET

Neuroinflammation is another outcome measure in this study and studied using PET imaging with a ^11^C-labelled R isomer of [1-(2-chlorophenyl)-N-methyl-N-(1-methylpropyl)-3-isoquinolinecarboxamide] ([^11^C]-(*R*)-PK11195), which binds to the 18-kDA translocator protein (TSOP) [43]. TSOP is upregulated in activated microglial cells and macrophages associated with neuroinflammation, but is expressed at low level in resting microglia [44]. Thus, [^11^C]-(*R*)-PK11195 can be used as a marker of inflammation specifically in brain.

PK11195-PET study is performed after a light meal. Before the PK11195-PET study, antecubital vein of the left hand is cannulated and fed-state blood samples for C-reactive protein and microglial cell quantification is taken in order to study possible correlations between these inflammation markers and PK11195-PET imaging results.

The participant is then positioned into the PET scanner (Discovery MI (DMI), GE Healthcare, US), in supine position with the brain in the scanning area of the gantry. The PET/computed tomography (CT) scanner used in the PK11195-PET study is the same scanner used in the FDG-PET study. Once the tracer of 350 MBq is injected into the vein, the scanning is started immediately and continued for 60 min in 2 × 15 s, 3 × 30 s, 3 × 60 s, 7 × 300 s, and 2 × 600 s time frames. Blood samples are not taken during the PK11195-PET scan. Images are reconstructed using the BSREM algorithm with BETA factor 350.

#### Magnetic resonance imaging and magnetic resonance spectroscopy

Magnetic resonance imaging (MRI) and proton magnetic resonance spectroscopy (MRS) studies are performed in the evening approximately four h after the lunch. Participants have a small snack before the study. The imaging is performed with Siemens Magnetom Skyra fit 3 T MRI system (Siemens Healthcare, Erlangen, Germany). MRI is performed in five parts as detailed below. Participants are allowed to have a break between the parts when necessary.

At first, the brain MRI is performed with a Siemens Head/Neck 20 channel coil, including brain morphology and the resting state functional MRI (fMRI) sequences. The brain protocol consists of six sequences as listed in Table 2 (localizer not listed). The resting state fMRI with eyes open is acquired twice.

**Table 2 Tab2:** Parameters of brain MRI sequences

Sequence	Slice orientation	Phase encoding direction	Number of slices	Field of view (mm^2^)	Slice gap (mm)	Voxel size (mm^3^)	Repetition time (ms)	Echo time (ms)	Inversion time	Flip angle (°)	Bandwidth (Hz/Px)	Imaging mode	Acceleration mode (factor)
T2 TSE	Transversal	R> > L	35	224 × 182	0.8	0.6 × 0.6 × 4.0	6600.0	89.0	N/A	150	224	2D	GRAPPA (2)
T1 MPRAGE	Sagittal	A> > P	192	256 × 240	N/A	1.0 × 1.0 × 1.0	2300	2.26	900	8	200	3D	GRAPPA (2)
FLAIR	Sagittal	A> > P	192	256 × 240	0	1.0 × 1.0 × 1.0	5000	386	1800	Variable	751	3D	GRAPPA (3)
Resting-state fMRI	Transversal	A> > P	48	220 × 220	0	3.4 × 3.4 × 3.4	3000	30	N/A	90	1562	2D	GRAPPA (2)
Field mapping	Transversal	R> > L	48	220 × 220	0	3.4 × 3.4 × 3.4	350	4.92; 7.38	N/A	60	290	2D	N/A

*TSE* Turbo Spin Echo, *GRAPPA* GeneRalized Autocalibrating Partial Parallel Acquisition, *MPRAGE* Magnetization Prepared RApid Gradient Echo, *FLAIR* Fluid-Attenuated Inversion Recovery, *fMRI* Functional Magnetic Resonance Imaging, *CAIPIRINHA* Controlled Aliasing in Parallel Imaging Results in Higher Acceleration, *HASTE* Half-Fourier Acquisition Single-shot Turbo spin Echo imaging, *VIBE* Volometric Interpolated Breath-hold Examination, *TRUFI* TRUe Fast Imaging with steady-state free precession

Secondly, a whole-body imaging is performed in order to define volume of adipose tissue in abdominal and femoral regions as well as volume of the liver and the pancreas. At first, a rapid whole-body localizer image is acquired using a FastView sequence utilizing a continuously moving table (table speed 46 mm·s^− 1^). Then, T1 VIBE Dixon images are acquired in five substeps which are 200 mm apart from each other (center to center). The general parameters of the series after the localizer sequences are listed in Table 3. A combination of Spine 32, Head/Neck 20, Body 30, Body 18 and Peripheral Angio 36 coil is used for signal acquisition.

**Table 3 Tab3:** Parameters of whole-body MRI sequences

Sequence	Slice orientation	Phase encoding direction	Number of slices	Field of view (mm^2^)	Slice gap (mm)	Voxel size (mm^3^)	Repetition time (ms)	Echo time (ms)	Respiration control (parts)	Flip angle (°)	Bandwidth (Hz/Px)	Imaging mode	Acceleration mode (factor)
FastView	Transversal	A> > P	1	480 × 420	5	5 × 5 × 5	2.56	1.44	none	N/A	801.3	2D	N/A
T1 VIBE Dixon	Transversal	A> > P	120	448 × 364	N/A	2 × 2 × 2	3.97	1.23; 2.46	Breath-hold (1)	9	1060	3D	CAIPIRINHA (4)

*VIBE* Volometric Interpolated Breath-hold Examination, *CAIPIRINHA* Controlled Aliasing in Parallel Imaging Results in Higher Acceleration

The third object is the heart, where pericardial fat volume is determined as well as the fat content within the septum by using MRS. The heart MRI protocol consists of 9 sequences as detailed in Table 4 (localizer sequences not listed) using a combination of Siemens Body 30 and Spine 32 coils. The first five sequences are used for positioning and planning of the two cine sequences to acquire them in four-chamber and short-axis orientations. T2 Haste sequence is used for positioning the breathing navigator voxel for the T1 turbo spin echo (TSE) dark blood sequence which is acquired for the analysis of pericardial fat volume. All sequences are acquired under breath holds. All but the T2 Haste and localizer are ECG triggered. In the cine sequences 30 frames were acquired in one ECG R-R interval.

**Table 4 Tab4:** Parameters of heart MRI sequences

Sequence	Slice orientation	Phase encoding direction	Number of slices	Field of view (mm^2^)	Slice gap (mm)	Voxel size (mm^3^)	Repetition time (ms)	Echo time (ms)	Respiration control (parts)	Flip angle (°)	Bandwidth (Hz/Px)	Imaging mode	Acceleration mode (factor)
TRUFI single shot axial	transversal	A> > P	10	340 × 252	6.0	1.3 × 1.3 × 6.0	295.68	1.23	Breath-hold (1)	38	849	2D	GRAPPA (2)
TRUFI single shot 2 chamber	2-chamber	L> > R	1	340 × 252	1.5	1.3 × 1.3 × 6.0	295.68	1.23	Breath-hold (1)	38	849	2D	GRAPPA (2)
TRUFI single shot nearly 4 chamber	nearly 4-chamber	A> > P	1	340 × 252	1.5	1.3 × 1.3 × 6.0	295.68	1.23	Breath-hold (1)	38	849	2D	GRAPPA (2)
TRUFI single shot short axis	short-axis	A> > P	1	340 × 252	1.5	1.3 × 1.3 × 6.0	295.68	1.23	Breath-hold (1)	38	849	2D	GRAPPA (2)
TRUFI single shot 4 chamber	4-chamber	A> > P	1	340 × 252	1.5	1.3 × 1.3 × 6.0	295.68	1.23	Breath-hold (1)	38	849	2D	GRAPPA (2)
Cine 4 chamber	4-chamber	A> > P	4	340 × 276	1.2	1.8 × 1.8 × 6.0	35.70	2.47	Breath-hold (4)	12	449	2D	GRAPPA (2)
Cine short axis	short-axis	A> > P	6	340 × 276	1.2	1.8 × 1.8 × 6.0	35.70	2.47	Breath-hold (6)	12	449	2D	GRAPPA (2)
T2 HASTE	Coronal	R> > L	30	400 × 400	1.0	1.6 × 1.6 × 5.0	1400	87	Breath-hold (2)	160	698	2D	GRAPPA (3)
T1 TSE dark blood	transversal	A> > P	20	340 × 276	2.0	1.3 × 1.3 × 4.0	750	4.1	Breath-hold (20)	180	849	2D	GRAPPA (3)

*TSE* Turbo Spin Echo, *GRAPPA* GeneRalized Autocalibrating Partial Parallel Acquisition, *HASTE* Half-Fourier Acquisition Single-shot Turbo spin Echo imaging, *VIBE* Volometric Interpolated Breath-hold Examination, *TRUFI* TRUe Fast Imaging with steady-state free precession

The fourth imaging region is the abdomen (Table 5, localizer sequences not listed), in which the fat content within the pancreas and the liver is determined by MRS using Spine 32, Siemens Body 30 and Siemens Body 18 coils. Finally, the fifth object is the tibialis anterior muscle measured with QED TxRx 15 channel knee coil (Table 6, localizer sequences not listed), in which intra- and extramyocellular lipid content is measured by MRS. Two MRS spectra are acquired from each organ (heart, pancreas, liver, tibialis anterior): one with water suppression and another without water suppression. For the heart, delay for the ECG trigger is adjusted for each participant, typical value being 210 ms. The general sequence parameters for MRS are listed in Table 7.

**Table 5 Tab5:** Parameters of liver and pancreas MRI sequences

Sequence	Slice orientation	Phase encoding direction	Number of slices	Field of view (mm^2^)	Slice gap (mm)	Voxel size (mm^3^)	Repetition time (ms)	Echo time (ms)	Respiration control	Flip angle (°)	Bandwidth (Hz/Px)	Imaging mode	Acceleration mode (factor)
T2 HASTE	Transversal	A> > P	49	380 × 309	1	0.7 × 0.7 × 5.0	1570.0	75; 420	Navigator	114	977	2D	N/A
T2 HASTE	Sagittal	A> > P	40	380 × 285	1	1.2 × 1.2 × 5.0	500.0	95	Navigator	160	710	2D	GRAPPA (2)
T2 HASTE	Coronal	R> > L	30	450 × 394	1	1.4 × 1.4 × 5.0	656.0	95	Navigator	160	710	2D	GRAPPA (2)

*HASTE* Half-Fourier Acquisition Single-shot Turbo spin Echo imaging, *GRAPPA* GeneRalized Autocalibrating Partial Parallel Acquisition

**Table 6 Tab6:** Parameters of the tibilais anterior muscle MRI sequences

Sequence	Slice orientation	Phase encoding direction	Number of slices	Field of view (mm^2^)	Voxel size (mm^3^)	Repetition time (ms)	Echo time (ms)	Flip angle (°)	Bandwidth (Hz/Px)	Imaging mode	Acceleration mode (factor)
T1 VIBE Dixon	Transversal	A> > P	144	268 × 201	1.4 × 1.4 × 1.0	4.14	1.23; 2.46	9.0	1040	3D	CAIPIRINHA (4)
T1 VIBE in-opp	Transversal	A> > P	160	192 × 156	1.0 × 1.0 × 1.0	4.76	1.51; 3.01	9.0	870	3D	None
T1 VIBE in-opp	Sagittal	A> > P	160	256 × 152	1.0 × 1.0 × 1.0	4.76	1.51; 3.01	9.0	850	3D	None
T1 VIBE in-opp	Coronal	R> > L	104	256 × 152	1.0 × 1.0 × 1.0	4.78	1.51; 3.01	9.0	850	3D	None

*VIBE* Volometric Interpolated Breath-hold Examination, *CAIPIRINHA* Controlled Aliasing in Parallel Imaging Results in Higher Acceleration

**Table 7 Tab7:** Parameters of the 1H MRS sequences in the heart (septum), pancreas, liver and tibialis anterior muscle

Sequence	Sequence type	Voxel size (mm^3^)	TE (ms)	TR (ms)	Number of signal averages	Bandwidth (Hz)	Number of datapoints	Water suppression	Water suppression bandwidth	Heartbeat control	Respiration control
Heart water-suppressed	PRESS	10 × 10 × 10	33	2000	128	2500	1024	Water saturation	35	ECG trigger	Navigator
Heart not water-suppressed	PRESS	10 × 10 × 10	33	2000	16	2500	1024	None	35	ECG trigger	Navigator
Pancreas water-suppressed	PRESS	15 × 15 × 10	30	4000	64	2500	1024	Water saturation	35	None	Navigator
Pancreas not water-suppressed	PRESS	15 × 15 × 10	30	4000	16	2500	1024	None	35	None	Navigator
Liver water-suppressed	PRESS	20 × 20 × 20	30	4000	32	2500	1024	Water saturation	35	None	Navigator
Liver not water-suppressed	PRESS	20 × 20 × 20	30	4000	4	2500	1024	None	35	None	Navigator
Tibialis water-suppressed	PRESS	12 × 12 × 20	33	4000	64	2500	1024	Water saturation	35	None	None
Tibialis not water-suppressed	PRESS	12 × 12 × 20	33	4000	16	2500	1024	None	35	None	None

#### Transthoracic echocardiography

Complete two-dimensional (2D), color, pulsed and continuous-wave Doppler echocardiogram is performed according to standard techniques. Conventional left-ventricular (LV) systolic function is measured with 2- and 4-chamber apical views (Simpson’s biplane method of discs, corrected for body surface area). LV end-diastolic volume index (EDVI), LV end-systolic volume index (ESVI) and LV ejection fraction (LVEF) are calculated. LV mass index is calculated using the area-length method as recommended by the American Society of Echocardiography and corrected for body surface area [45]. Advanced LV systolic function parameters are measured with tissue Doppler imaging (TDI). Peak systolic tissue velocities are derived from septal and lateral pulsed wave and color coded TDI. Speckle tracking derived strain parameters are obtained from apical 4,2 and 3-chamber views [46].

Conventional LV diastolic function parameters are derived from 2- and 4-chamber views [47]. Maximum left atrium (LA) volume is derived with discs method, corrected for body surface area. Pulsed wave Doppler velocities are measured from the apical 4-chamber view using a 2 mm sample volume positioned at mitral leaflet tips. Transmitral early (E wave) and late (A wave) diastolic velocities are measured as well as E wave deceleration time. Pulsed wave TDI of the lateral and septal mitral annulus are used to measure E’.

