Given that the response to exercise training is heterogeneous and affected by genetic factors, this study utilizes a co-twin control method in order to exclude the confounding effects of genetic factors. To pursue this objective, we recruit monozygotic (MZ) twin pairs that are discordant for body mass index (BMI) (difference ≥ 2 kg•m^− 2^) and at least the other twin is overweight (BMI ≥ 25 kg•m^− 2^). MZ twins share same genes at sequence level, are of the same sex, age and share most of their childhood environment. Thus, they provide an ideal research design to study the effects of regular exercise training on physical performance and metabolic health outcomes, in which the confounding effects of genetic factors can be controlled [22]. Additionally, because twin pairs included into this study are discordant for BMI, it is possible to examine the interaction-effect of different baseline weight and long-term exercise while genetic factors are controlled.

Exercise training provides an effective protection against chronic diseases that are triggered by low-grade systemic inflammation, such as insulin resistance [23]. As a drug-free treatment option, exercise training could lead to significant reduction in treatment cost due to reduced need for medication and fewer complications due to the improved physical fitness. We have previously shown in the Turku PET Centre that only 2 weeks of exercise training has a positive effect not only on the metabolism of the skeletal muscle [24] but also that of the heart [25, 26], the brain [27], and the intestine [28] in healthy, insulin resistant or type 2 diabetic participants. We have also shown that short-time exercise training decreases ectopic fat in the pancreas [29], liver [30], in and around the heart [31] and increases microbial diversity and decreases microbiota content related to obesity and intestinal inflammation [32]. These short-term intervention studies suggest that already a short exercise training period exerts positive systems-level effects on the metabolism of various tissues. Thus, current evidence provided by our research group and others’ [33, 34] suggest that exercise is able to counteract the undesired disturbances in metabolism related to obesity and T2D. However, more specified evidence of the effects of exercise training on different tissues is still needed in overweight/obese people prone to develop metabolic diseases such as T2D.

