### Participants

The participants of the CROSSYS study are monozygotic (MZ) twin pairs that are recruited from three unique population-based longitudinal twin studies [35–37]. Of these three cohorts, the two younger cohorts consist of twins from the FinnTwin12 (FT12, twins born 1983–1987) and FinnTwin16 (FT16, twins born 1975–1979) studies, and twins born in 1945–1957, who form part of the older cohort from the Finnish Twin Cohort Study, twins born in 1945–1957 (Fig. 2). The three cohorts consist altogether of more than 9200 twin pairs, of which 1/3 are MZ. All twins have been identified through Finland’s central population registry, permitting exhaustive and unbiased ascertainment of all twins living and resident in Finland. A total of 54 MZ pairs discordant for BMI and/or insulin resistance have participated previously to the TwinFat study in the University of Helsinki, and their monozygocity has been confirmed by the genotyping of 10 informative genetic markers [38]. All these 54 pairs are invited to participate in the present study. Inclusion criteria are: MZ twins, BMI within-pair difference ≥ 2 kg•m^− 2^ and/or insulin resistance, and at least one of the co-twins is overweight (BMI > 25 kg•m^− 2^). Exclusion criteria are: BMI > 60 kg•m^− 2^, body mass > 170 kg, waist circumference > 150 cm (due to the gantry limitations of PET and MRI machines), mental disorder or poor compliance, eating disorder or excess use of alcohol, active ulcus disease, diabetes requiring insulin treatment or fasting glucose > 10 mmol•l^-1^, pregnancy, past dose of radiation, claustrophobia, presence of ferromagnetic objects that would make MRI contraindicated, physical disability that would prevent exercising, or any other ﻿condition which could potentially endanger participant’s health during the study or interfere with the interpretation of the results. It is estimated that 25% of twins do not want to participate or are not eligible to the study and another 25% will drop out during the intervention. Hence, 30 twin pairs are expected to successfully complete the study.

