#### Statistical analysis

The data is first evaluated visually based on standard techniques including quantile-quantile plots and histograms to detect possible outliers and to assess the normality. Normality is also evaluated using Shapiro-Wilk test and logarithm or other statistical transformations are performed when appropriate. The data is also analyzed for possible dimensionality reduction using standard methods such as principal component analysis.

Statistical analyses are performed using hierarchical mixed linear models. The models include two within-factors: time (before and after intervention) and twin (heavier and leaner co-twin), and their interaction term (time x twin). Medications, adherence to the exercise intervention, sex, age, BMI and other factors are included in the models when appropriate. The potential covariates will be screened for association, and covariates that do not show significant association with the response variable will be excluded from the analysis. When the number of participants allows it, we will carry out separate subgroup analyses by sex, age (two younger cohorts vs. older cohort), and/or mass (obese vs. non-obese participants). Subjects with missing data points are included in the statistical analysis by using the restricted maximum likelihood estimation within the linear mixed models. Hence, model-based means and 95% confidence intervals are reported.

Correlation analysis are performed using Pearson’s product-moment correlation coefficient for normally distributed data and Spearman’s rank correlation coefficient for non-normally distributed data. All statistical tests are performed as two-sided and *p*-values less than 0.05 will be considered as statistically significant.

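### Body-surface-area indexing of LV volumes, LV mass and LA volume puts the weight contrast under study into the denominator of the heavier-versus-leaner comparison

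*Protocol article*

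**What the plan says.** Under Transthoracic echocardiography, the Protocol article measures LV volumes with "Simpson’s biplane method of discs, corrected for body surface area" and then states that "LV end-diastolic volume index (EDVI), LV end-systolic volume index (ESVI) and LV ejection fraction (LVEF) are calculated". For LV mass it says "LV mass index is calculated using the area-length method as recommended by the American Society of Echocardiography and corrected for body surface area", and for the atrium "Maximum left atrium (LA) volume is derived with discs method, corrected for body surface area". No unindexed or height-indexed form of these four measures is named, and no BSA formula is given.

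The Participants section reads "Inclusion criteria are: MZ twins, BMI within-pair difference" of at least 2 kg/m² and/or insulin resistance, with at least one co-twin overweight. The Background describes the matching: "MZ twins share same genes at sequence level, are of the same sex, age and share most of their childhood environment".

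Under Statistical analysis, "The models include two within-factors: time (before and after intervention) and twin (heavier and leaner co-twin), and their interaction term (time x twin"). The same section adds: "Medications, adherence to the exercise intervention, sex, age, BMI and other factors are included in the models when appropriate". Covariates without a significant association with the response are dropped.

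**The concern.** In unrelated people, dividing by BSA removes body-size variation that is usually a nuisance. In this design, matching on genes, sex and age has already removed much of it. If co-twins are also of similar height, the within-pair difference left in BSA is mostly the weight difference that defines heavier and leaner.

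Two co-twins with identical hearts would then get different index values, with the lower one in the heavier twin. An enlargement of the ventricle or atrium that truly accompanies excess weight would be shrunk, hidden or turned into an apparent reduction. The Discussion presents the effect of obesity free of genetic confounding as the study's main strength, so this contrast should not have weight built into its outcome scale. If weight also changes during training, the same denominator moves the before-after comparison. If it changes by different fractions in the two twins, it moves the interaction too.

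**Working it through.** The protocol gives no figure for the echocardiographic indices, so there is nothing to reproduce. The check asks what the BSA denominator does when the heart is held constant.

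**Inputs from the protocol**
- Scaling to BSA (Transthoracic echocardiography).
- BMI gap of at least 2 kg/m² and/or insulin resistance (Participants).
- Minimum 22 pairs (Power calculation) and 30 expected completers (Participants).
- Two-sided 0.05 (Statistical analysis).

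**Assumptions, not in the protocol**
- Equal height within a pair.
- BSA by Mosteller, √(height × weight / 3600), or by DuBois, 0.007184 × weight^0.425 × height^0.725.
- The BMI pairs, weight losses and SDs shown below.

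**Between co-twins.** With the same heart and height, index(heavier) / index(leaner) = BSA(leaner) / BSA(heavier) = (BMI leaner / BMI heavier)^k, with k = 0.5 (Mosteller) or 0.425 (DuBois). Height cancels.

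| BMI leaner vs heavier | Mosteller | DuBois |
|---|---|---|
| 23 vs 25 | −4.1% | −3.5% |
| 25 vs 27 | −3.8% | −3.2% |
| 30 vs 32 | −3.2% | −2.7% |
| 34 vs 36 | −2.8% | −2.4% |
| 25 vs 28 | −5.5% | −4.7% |
| 25 vs 31 | −10.2% | −8.7% |
| 30 vs 36 | −8.7% | −7.5% |

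Example: an assumed LV mass of 150 g in both twins at 170 cm gives, by Mosteller, 81.2 vs 78.1 g/m² at BMI 25 vs 27, and 81.2 vs 72.9 g/m² at 25 vs 31.

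**Masking a true effect.** Suppose the heavier twin's LV mass is truly 8% larger at BMI 25 vs 31. The index ratio is 1.08 × 0.898 = 0.970 (−3.0%) by Mosteller and 1.08 × 0.913 = 0.986 (−1.4%) by DuBois. The sign reverses under both.

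**Before-after.** With the same heart and fractional weight loss L, the index changes by (1 − L)^(−k) − 1.

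| Weight loss | Mosteller | DuBois |
|---|---|---|
| 0% | 0 | 0 |
| 2% | +1.0% | +0.9% |
| 3% | +1.5% | +1.3% |
| 5% | +2.6% | +2.2% |

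If, for illustration, the heavier twin lost 5% and the leaner 2%, time x twin would carry about 2.6 − 1.0 = 1.6 percentage points (Mosteller) or 2.2 − 0.9 = 1.3 (DuBois).

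**Chance that the artefact alone is significant.** Paired normal approximation: Φ(artefact × √n / SD − 1.96), where SD is that of the within-pair percentage difference. It counts only rejections in the artefact's direction and applies one gap to all pairs.

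| Artefact | Pairs | SD 8% | SD 12% | SD 16% | SD 20% |
|---|---|---|---|---|---|
| 3.8% (25 vs 27, Mosteller) | 22 | 0.61 | 0.32 | 0.20 | 0.14 |
| 3.8% | 30 | 0.74 | 0.41 | 0.25 | 0.18 |
| 10.2% (25 vs 31, Mosteller) | 22 | 1.00 | 0.98 | 0.85 | 0.67 |
| 10.2% | 30 | 1.00 | 1.00 | 0.94 | 0.80 |
| 1.5% (before-after, 3% loss) | 22 | 0.14 | 0.08 | 0.06 | 0.05 |
| 1.5% | 30 | 0.18 | 0.10 | 0.07 | 0.06 |

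**After the fix.** With unindexed values, an identical heart gives a 0% between-twin difference, and an unchanged heart gives 0% before-after whatever the weight change. A height-based index does the same, for the between-twin contrast at equal height.

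**The case against.** **The section describes measurement.** It says which indices are calculated. It does not say that raw values are discarded or that the index alone enters the model. A reader might infer that only the BSA-indexed form will be analysed, but the protocol does not say so, and raw values must exist before indexing. This objection stands. What remains is that the indexed form is the only one named for these four measures.

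**The outcomes are peripheral.** The stated primary outcomes are tissue-specific glucose uptake and M-value, and the systems listed under Study design include no LV mass, LV volume or LA volume. LVEF is a ratio in which BSA cancels. Tissue velocities, strain, transmitral velocities and deceleration time are not indexed. So the point concerns four measures and not the study's cardiac assessment as a whole.

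**Weight may stay stable.** A reader might infer that the index will show a before-after difference in an unchanged heart. The protocol does not support that. It neither targets nor quantifies weight loss, participants are asked to keep their diet, and excessive loss from reduced intake is discouraged. The artefact is zero at stable weight, and a 1.5% shift would seldom be significant. The between-twin artefact is present at baseline regardless.

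**The heavier twin need not always score lower.** That depends on near-equal height, which the protocol does not state, and on a BMI gap, which pairs admitted for insulin resistance need not have.

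**BSA indexing is conventional and answers a real question,** namely whether the heart is large for the body. That is fair, and a heavier twin's larger heart may be proportionate. But whether excess weight or training changes the heart is a different question, and the index alone does not answer it. The optional BMI covariate does not either: it conditions on the exposure and may be dropped at screening.

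**Conclusion.** The concern holds for the heavier-versus-leaner contrast in LV end-diastolic volume, LV end-systolic volume, LV mass and LA volume. With near-equal co-twin height and identical hearts, the heavier twin's index is lower by about 2.4–4% at a 2 kg/m² gap, depending on BMI level and BSA formula, and by about 9–10% at BMI 25 versus 31. The direction does not depend on the BSA formula or the SD.

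At BMI 25 versus 27 (Mosteller), the chance that the artefact alone is significant runs from about 0.14 (22 pairs, SD 20%) to 0.74 (30 pairs, SD 8%). This range is wide because the SD is assumed. The larger gaps are illustrative too, since the protocol gives no distribution of BMI differences.

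The time and time x twin effects are conditional: about 1–3% upward for a 2–5% weight loss, and nothing without weight change. The primary outcomes are untouched. This is a cheap improvement to secondary cardiac measures and does not threaten the trial's main conclusions.

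**What to change.** State in the analysis plan that, for LV end-diastolic volume, LV end-systolic volume, LV mass and LA volume, the twin, time and time x twin effects are estimated on unindexed values (ml, g) or on height-based indices. Report the BSA-indexed results alongside, interpreted as heart size relative to body size, and name the BSA formula used.

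The cost is about two sentences and a few extra analyses. The unindexed values exist before indexing, and height is already needed for BMI and BSA, so no new measurement is required. The small downside is that unindexed or height-indexed values are less directly comparable with BSA-based reference limits. Reporting both scales covers this.
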